## Abstract

**Background:**

Increasing choice among HIV pre-exposure prophylaxis (PrEP) products bears potential to increase uptake, persistence, and coverage amongst those at risk of HIV acquisition. Few studies have evaluated PrEP persistence during real-world delivery of multiple PrEP products from community-based sites to adolescents and young people.

**Methods:**

The PrEPared to Choose (PtC) study delivers PrEP choice across oral, injectable, and vaginal ring options to adolescents and young people (15–29 years) and their potential male partners in Cape Town, South Africa. This phase 3B clinical trial utilizes a type 2 hybrid implementation design with co-primary clinical and implementation aims that include an analysis of PrEP persistence (defined as sustained use of PrEP product as intended with < 7 vs. < 28 day gap in dosing as scheduled) over the short term (7 months) and long term (18 months), and the identification of implementation strategies that best support PrEP adoption and persistence. PtC is delivered from a mobile clinic and a public health primary care clinic, staffed by trained nurses, HIV counsellors, and peer-navigators. PrEP selection is guided by a co-created PrEP choice counselling intervention, with allowance for product switching at subsequent visits, but no reimbursement for PrEP uptake or return.

**Discussion:**

PrEPared to Choose will provide an early report of real-world PrEP choice delivery, including all three currently available and approved modalities. The protocol is designed to simulate a real-world environment that provides insight into likely PrEP persistence patterns and practical challenges to PrEP choice implementation in a high HIV burden setting (South Africa) and within high HIV incidence populations (adolescents and young people). The results will be used to inform PrEP choice delivery in South Africa and build a framework into which future, emerging PrEP modalities can be incorporated.

**Trial approvals and registration:**

This is a phase 3B clinical trial registered with the South African Health Products Regulatory Authority (20230904). Ethical approval was granted by the Human Research Ethics Committee (Faculty of Health Sciences, University of Cape Town, 567/2023). It is registered with the South African National Clinical Trial Registry (DOH-27-012024-5189, 26 January 2024) and ClinicalTrials.gov (NCT06807736, retrospectively registered on 4 February 2025).

## Background

HIV pre-exposure prophylaxis (PrEP) formulations have expanded in recent years, moving from a single daily, oral tablet option to include a monthly intra-vaginal ring (DapiRing) and a two-monthly intramuscular injection (Cabotegravir long-acting, CAB LA), with further long-acting options imminently anticipated [1–4]. As occurred with contraceptive choice, the introduction of PrEP choice is expected to increase PrEP uptake, persistence, and ultimately HIV exposure coverage. This is predominantly because new formulations stand to mitigate challenges with daily adherence and pill burden previously reported by oral PrEP users [1, 5]. 

South Africa (SA) has one of the largest HIV epidemics globally, with 5.8 million people on treatment and 149 000 new infections in 2023 [6]. The benefits of primary HIV prevention are both to the individual, who avoids a lifetime of treatment and HIV-associated sequelae, and the state that must otherwise fund an expensive HIV treatment and care programme. Increasing PrEP coverage requires an increased product uptake as well as increased persistent use, both of which have been historically sub-optimal when oral PrEP alone was available, despite high efficacy, safety, and widespread availability in local SA primary care clinics to anyone that perceives themselves at risk of HIV infection [1, 3]. 

The burden of new HIV infections in SA is primarily amongst adolescents and young people, particularly adolescent girls and young women and gender and sexually diverse populations [7, 8]. There is, however, increasing acknowledgment of the need to engage male partners, who have historically shown low uptake of HIV testing and prevention interventions [9]. Men, adolescents, pregnant and breastfeeding women, and young people have historically shown poor uptake of oral PrEP, yet indicate a theoretical preference for long-acting formulations and so stand to benefit from expanded PrEP options [10–15]. 

The REACH study investigated adherence to oral PrEP and the DapiRing amongst sub-Saharan African adolescent girls and young women [16]. This open-label study showed higher adherence to oral PrEP and DapiRing compared to previous trials, with most participants preferring the longer-acting DapiRing due to its lower user burden [16]. This provides support for the hypothesis, to be tested in the ongoing PrEPared to Choose (PtC) study, that expanding PrEP choice may improve PrEP adherence and ultimately increase HIV prevention coverage to reduce overall HIV acquistion [16]. With the DapiRing and a two-monthly injectable PrEP (Cabotegravir long-acting, CAB LA) approved for HIV prevention in SA for in 2022 [16, 17], there is an urgent need to deliver PrEP choice to adolescents, young people, and their intimate partners, in a manner that builds on the lessons of oral PrEP implementation and that reaches the populations most likely to benefit.

## Study design

PtC seeks to describe patterns of persistence of HIV PrEP products, individually and overall, amongst a cohort of South African adolescents and youth (aged 15–29 years) when offered different PrEP modalities (oral vs. DapiRing vs. injectable) within a sexual and reproductive health service (SRH) package and supported by comprehensive choice counselling. PtC will probe implementation barriers and enablers in PrEP adoption (decision to use any PrEP product), initiation (first dose of any PrEP product), and persistence amongst both PrEP users and PrEP providers (specialised nurses and HIV counsellors) in real-world government primary health care facilities and mobile clinic settings. PtC utilises a hybrid implementation design with co-primary implementation and clinical aims, in the form of a non-randomised, quasi-experimental trial design.

### Aims and objectives

The primary clinical aim of PtC is to describe patterns of short and long-term persistence (as measured over 7 months and 18 months respectively) across three HIV PrEP products, individually and overall, amongst a cohort of South African adolescents and youth. Participants are offered a choice between PrEP products, following HIV testing and comprehensive choice counselling. PrEP products include (a) oral PrEP (Emtricitabine/tenofovir), prescribed as a daily tablet or for event-driven use for select male participants; (b) a Dapivirine-containing vaginal ring (DapiRing) that requires monthly replacement, for non-pregnant and non-breastfeeding adolescent girls and young women; and (c) Cabotegravir long-acting (CAB-LA) as a two monthly intra-muscular gluteal injection.

PrEP persistence is defined as sustained, continuous use of the selected product as intended, with consideration of both (a) a < 7-day gap in PrEP availability for daily dosing (oral PrEP), DapiRing insertion, or subsequent injection or (b) a < 28-day gap. The 7-day gap between the scheduled return vs. actual return is consistent with the definitions used in CAB-LA phase 3 clinical trials [17]. – [18] The 28-day gap follows South African recommendation guidelines for a “missed visit” and is the clinical time point where re-initiation on CAB-LA would be needed. In the South African context, it is expected that the 28 day gap will provide a more realistic timeframe for return. In addition to a missed visit, non-persistence on a specific product is further defined as any participant that switches to using another PrEP product with (a) < 7 days and (b) < 28-day gap between products. PrEP persistence in the cohort, by product and on PrEP overall, will be calculated and reported at 7 months (short-term persistence) and 18 months (long term persistence). The comparison of PrEP persistence by product will be related to the hypothesis that there will be a significantly greater persistence in the CAB LA group compared to oral PrEP and/or DapiRing.

The primary implementation aim is to determine what combination of implementation strategies best achieve PrEP adoption (decision to use any PrEP product), active implementation (PrEP initiation), and persistence (sustained PrEP use) outcomes within a RE-AIM (Reach, Effectiveness, Adoption, Implementation, Maintenance) implementation science framework. This will be assessed over the short term (7 months) and long term (18 months), considering barriers and enablers for both the PrEP user and PrEP provider. Mixed qualitative and quantitative methods and process evaluations will be used to inform the implementation analysis.

Several secondary aims and an exploratory aim are described in Table 1.

**Table 1 Tab1:** An overview of PtC study primary and secondary aims, including their endpoints and time of measurement

Aim	Endpoint (s)	Time of measurement
*Primary Aims*		
1.1 To compare short term persistence (over 7 months) across PrEP modalities and PrEP overall (*Clinical aim)*	Persistence - defined as sustained, continuous use of the selected PrEP product as intended, with consideration of both (a) a < 7 day gap or (b) a < 28 day gap in PrEP provision for daily dosing (oral PrEP), DapiRing insertion, or subsequent injection. Participants that product switch are considered *PrEP persistent overall* but not *PrEP product persistent*. Product use patterns, including product switches and re-starts, are tracked for the full 7-month period for all persistent and non-persistent participants.	7 months from PrEP initiation.
1.2 To determine what combination of implementation strategies best achieve PrEP adoption and persistence over the short term within a RE-AIM framework (*Implementation aim).*	*Reach* – (i) time to recruit the injectable PrEP study population (*n* = 900 participants); (ii) demographic and clinical characteristics of PrEP initiators vs. persistent users vs. non-persistent users in each PrEP product user group. *Effectiveness* – (i) frequency and description of PrEP product reported side effects; (ii) frequency and description of reported social harms, including intimate partner violence. *Adoption* – (i) proportion of participants reached and sustained at mobile clinic vs. government facilities; (ii) frequency, timing, and nature of product switches and PrEP discontinuation, informed by a qualitative assessment of reasons for non-persistence. *Implementation* – (i) description and evaluation of PrEP choice counselling delivery as per counselling time per person, fidelity assessment scores, and correlation of documented counselling outcomes with actual PrEP persistence; (ii) Evaluation of injectable PrEP administration according to clinical operating procedures. *Sustainability* – (i) sustainability of PrEP choice delivery at participating sites as assessed through the clinical sustainability assessment tool and (ii) qualitative assessment of acceptability and readiness to receive future long-acting PrEP products.	All participants having passed through (a) 7 months and (b) 18 months of study participation.
*Secondary Aims*		
2.1 To compare long term persistence (over 18 months) across PrEP modalities and PrEP overall (*Clinical aim)*	As above for aim 1.1.	18 months from PrEP initiation.
2.2 Time on PrEP based on expected (injections given; product collected) vs. actual (self-reported patterns of use) PrEP coverage *(Clinical aim*)	Total time on PrEP overall based on oral/vaginal PrEP collection and injections vs. self-reported patterns of use. Actual time and self-reported time on PrEP for injectable PrEP users is equivalent.	7 months and 18 months from PrEP initiation.

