#### PrEP providers and their role

PrEP delivery in SA is nurse-driven and delivered, with PrEP dispensing allowable for any Nurse-Initiated Management of Antiretrovirals (NIMART) qualified practitioner. PtC is delivered by a team of PrEP providers that include NIMART qualified nurses, HIV counsellors, and peer navigators (trained youth aged 18–29 from the study area) [21]. At both the mobile and clinic setting, potential participants are welcomed by peer navigators who provide general HIV health promotion talks and information about the study. Interested participants are seen by the HIV counsellor, following registration and consent procedures, who conduct HIV testing and PrEP choice counselling (average time 30 min) for all HIV negative participants.

Participants are then referred for a nurse-led clinical assessment for eligibility to use the PrEP product of choice and PrEP administration. Administration involves injection of CAB-LA, provision (and insertion if requested) of the DapiRing, or provision of a 30-day oral PrEP supply. All participants are required to return at one month post PrEP initiation to assess safety and interest in continuation on the product and receive their second loading CAB-LA injection or a three-month supply of oral PrEP or DapiRing. All members of the team are trained in adolescent and gender friendly health care and good clinical practice.

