#### Oral PrEP

Oral PrEP is currently standard of care in SA and this study follows national oral PrEP guidelines with regards to counselling and administration [23, 24]. A notable difference is the promotion of event-driven PrEP for male participants, whereby oral tablets are taken in a 2-1-1 formation (two tablets 2–24 h prior to potential HIV exposure and then continue one tablet daily until two days after the last potential exposure). Event-driven PrEP is not part of national PrEP guidelines but is widely supported and expected to be introduced into updated national guidelines expected in 2025.

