#### CAB-LA administration

CAB-LA is delivered in a long-acting suspension via an intramuscular injection every eight weeks, as a 3 ml injection containing 600 mg of Cabotegravir [26]. Administration is performed by a NIMART qualified professional nurse trained in antiretroviral drug delivery and in the appropriate injection technique. All sites are equipped with resuscitation equipment and trained in basic life support, with participants required to remain on site for a 10-minute observation period post-injection. A second initiation dose is provided at 1 month. Participants are required to return for that scheduled visit within 28 days in order to continue the schedule. Those that return more than 28 days after the scheduled visit (i.e. >56 days after the first injection) are required to re-start the injection schedule. Thereafter, injections are given every 8 weeks with specific guidelines to support continuation after missed injections (< or > 4 weeks since target injection date) [26]. 

For both oral PrEP and DapiRing, a single month’s supply (one tablet bottle or one ring) is supplied at the initiation visit and the participant is required to return after one month to assess product suitability and sustained use. If the participant selects to continue with this product, they are provided with a three-month supply (three tablet bottles or three DapiRing products). This reduces the overall number of clinic visits required for oral and ring participants compared to injectable PrEP, which necessitates in-person visits at least every 2 months. Oral and ring PrEP users may further opt to receive their next supply via courier. In the courier package, they receive an HIV self-test, instructions on how to do the test and where to send results. Access to subsequent courier deliveries is dependent on disclosure of HIV self-testing results.

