PtC has purposefully included a broad population range of adolescent and young people, including heterosexual males and gender and sexually diverse populations, rather than tailoring the service to adolescent girls and young women (a traditional PrEP target in the Eastern/Southern African setting). This was pursued intentionally to firstly, reduce stigma that can arise from only offering PrEP to a single population designated to be high risk, and secondly, to allow for a description of natural PrEP uptake rates among different populations when offered as a generalised service to young people. The resulting data will be used to inform which populations can be accessed through generalised services and which populations may need dedicated outreach interventions and spaces. Where possible, peer navigators from sexual and gender diverse groups have been employed.

The introduction of injectable PrEP, CAB-LA, has been broadly anticipated to alter the PrEP landscape, increasing both uptake and persistence. However, CAB-LA use up until this point has only been described in the context of clinical trials where robust eligibility criteria, study reimbursement, and strict visit schedules likely influenced the rate of on time return for subsequent injections. On time return in these studies was described as within a 7-day window [17, 18]. In the South African context, this is broadly considered to be unrealistic due to several factors including participant challenges with transport, inflexible work schedules, and community safety concerns. It is hypothesized that a more flexible 28-day visit window is likely to allow an improved rate of return and persistence, while still operating within the bounds of clinical safety and PrEP product efficacy. The PtC study as such will report on persistence using both a 7 day and 28-day visit window to highlight the impact of this on reported persistence outcomes.

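### The oral persistence gap is set for daily dosing and scheduled return, so it does not measure persistence in men using the event-driven oral PrEP that the trial promotes

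*Protocol article*

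**What the plan says.** Under Aims and objectives, the protocol article describes oral PrEP as "prescribed as a daily tablet or for event-driven use for select male participants". The next paragraph defines persistence as continuous use of the chosen product as intended, with "a < 7-day gap in PrEP availability for daily dosing (oral PrEP), DapiRing insertion, or subsequent injection" or a gap under 28 days. Table 1 repeats the rule as a "gap in PrEP provision for daily dosing (oral PrEP), DapiRing insertion, or subsequent injection".

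The same section says how the gap is measured. It refers to "The 7-day gap between the scheduled return vs. actual return", takes the 28-day limit from a national missed-visit guideline, and treats a missed visit as non-persistence. The Discussion says that the study "will report on persistence using both a 7 day and 28-day visit window".

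The Oral PrEP section names as a departure from national guidelines "the promotion of event-driven PrEP for male participants, whereby oral tablets are taken in a 2-1-1 formation". The supply schedule is not split by dosing mode: PrEP providers and their role gives "provision of a 30-day oral PrEP supply" at initiation, and CAB-LA administration gives three bottles after the one-month visit. Neither the gap rule nor the return date has a separate provision for event-driven users.

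**The concern.** Scheduled return is a reasonable marker of the end of cover when one tablet is taken each day. It is not one when tablets are taken around exposures, because the supply then lasts for as long as the exposure pattern dictates. The rule names one dosing mode while the trial promotes two within the same product group.

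Oral versus CAB-LA persistence is a stated primary comparison, with the hypothesis that CAB-LA is higher. The Statistical analysis section keeps everyone who started oral PrEP in the oral denominator, so event-driven users are pooled with daily users. A late return with tablets in hand would also enter the Kaplan-Meier and Cox analyses as a discontinuation. The analyses are to be repeated in male subgroups, where the ring is not available and oral PrEP is the only comparator for CAB-LA.

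**Working it through.** The plan gives no figure on this point. The nearest scale is the sample size paragraph, which targets differences of 8 points, or 11 points with 700 on CAB-LA and 200 on oral PrEP.

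**Inputs from the article.** 2-1-1 for one exposure day: 2 + 1 + 1 = 4 tablets. Supply: one month, then three months. Windows: a gap of 7 days or more, or of 28 days or more, fails.

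**Assumptions.** 30 tablets per bottle (28 also checked, since the Statistical analysis section mentions a 28-day regimen); return due when a daily supply would end; isolated exposures; first exposure on the day of supply; no tablets carried over. Exposure frequency is not given, so it is varied.

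**Formula.** Courses = tablets / 4, rounded down. First exposure without a full course = courses × days between exposures.

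| Supply | Exposure | Courses | First uncovered exposure | Return due | Late by <7 rule but covered | Late by <28 rule but covered |
|---|---|---|---|---|---|---|
| 30 | weekly | 7 | 7 × 7 = day 49 | day 30 | days 37–48 | none (late from day 58) |
| 30 | fortnightly | 7 | 7 × 14 = day 98 | day 30 | days 37–97 | days 58–97 |
| 90 | weekly | 22 | 22 × 7 = day 154 | day 90 | days 97–153 | days 118–153 |

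In the last row the man still holds an unused full course up to day 146. From day 147 to 153 he is using, or has just used, his last one, and no exposure has gone uncovered. With the refill at about day 30, days 118–153 are study days 148–183, inside the 7-month endpoint. With 28-tablet bottles the refill gives 84 / 4 = 21 courses and a first uncovered exposure at 21 × 7 = day 147. Return is due at day 84, so days 112–146 fail both windows.

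**The opposite case.** At two isolated exposures a week (8 tablets a week), a 90-tablet refill covers 22 × 3.5 = 77 days. A man returning on day 90 is on time, yet has gone 90 − 77 = 13 days without a full course, which is a gap over 7 days that the rule does not see. If he returns on day 117 he is 27 days late and passes the 28-day rule, with 117 − 77 = 40 days uncovered. On the first bottle the shortfall is only 30 − 7 × 3.5 = 5.5 days. If exposures are close enough for courses to run together, use falls back to about 7 tablets a week and schedule and supply agree.

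**Where the rule changes direction.** Ignoring whole-course rounding, tablets outlast the 28-day window at or below 90 / 118 × 7 = 5.3 a week on a refill, and at or below 30 / 58 × 7 = 3.6 a week on the first bottle.

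**Scale.** With 200 oral starters, each man reclassified moves oral persistence by 1 / 200 = 0.5 points. For illustration only, suppose true persistence is 50%, half of the persistent event-driven users are wrongly classed non-persistent, and none is misclassified the other way. An event-driven share of 10%, 20% or 30% then lowers oral persistence by 0.5 × 0.5 × share = 2.5, 5 or 7.5 points. None of these inputs comes from the article.

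**The case against.** A uniform visit rule is defensible. Every participant must return at one month, HIV testing is done at each visit, and a late return is a real lapse in the service whatever the tablet count. This stands for the first bottle: a weekly user who returns on day 45 missed a required visit by 15 days, and still passes the 28-day rule, which the article considers the more realistic one. It is less convincing after the refill, where the same use fails both windows, and the endpoint is worded as use of the product rather than attendance.

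The phrases about intended use and availability could be read to protect a man with tablets in hand. But the sentences that follow measure the gap by return date and count a missed visit as non-persistence.

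Oral users also need fewer visits than CAB-LA users and may use a courier, which gives them fewer chances to be late. That is true, but it is a separate influence and does not correct this one.

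A condensed article may leave dosing-mode detail to the full protocol or analysis plan. Here, however, the article states the definition twice and names daily dosing each time, so an event-driven rule elsewhere would depart from it.

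Finally, the analysis in adolescent girls and young women is free of the problem, and aim 2.2 compares product collection with self-reported use. Both help interpretation, but neither repairs the pooled oral versus CAB-LA comparison or the male subgroups.

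**Conclusion.** The point holds as a misfit between the stated primary definition and a regimen that the trial promotes. At about one exposure a week or fewer, a man with cover in hand can be classed non-persistent; after a three-bottle refill this happens under both windows. At two isolated exposures a week, a true gap can be missed.

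A reader might infer that the rule can only lower oral persistence and so systematically favours the CAB-LA hypothesis. The article does not support that. The twice-weekly case runs the other way, and neither exposure frequency nor the number of event-driven users is given. The net direction and size are therefore unknown, and the 2.5 to 7.5 points above are not an estimate. What can be said is conditional: if use is mostly less than weekly, oral persistence is understated against CAB-LA, most visibly in the male subgroups. Men who return on schedule and use no more than a daily supply are unaffected.

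The day counts rest on the tablet and schedule assumptions listed; using 28-tablet bottles does not change the conclusion. This should be fixed, but it does not undermine the trial as a whole.

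**What to change.** - In Aims and objectives and Table 1, limit the daily-dosing gap to daily oral users.
- Record dosing mode (daily or event-driven) at each dispensing.
- Report daily and event-driven oral users in separate rows.
- Name as a sensitivity analysis the CAB-LA versus oral comparison (chi-square, Kaplan-Meier and Cox) without event-driven users.
- Where tablets left are recorded at return, or at the follow-up contact already made when a visit is more than 7 days late, also report event-driven persistence as still choosing event-driven use and holding at least one full course (4 tablets). This works better as a supplementary measure than as the primary rule, because the study is already running.

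The cost is one or two REDCap fields and no extra visits. The oral group is smaller in the sensitivity analysis, and tablets-left data may be missing for participants already enrolled.

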#### Statistical analysis

PrEP initiation in this study is defined as having received a 28-day regimen of oral PrEP tablets, receiving a DapiRing, or receiving a CAB-LA injection depending on the respective product choice. Initiators are participants that have selected a specific PrEP product at baseline after receiving PrEP choice counselling.

To determine the primary and secondary endpoints of short-term and durable persistence (as defined above), a Cox proportional hazards model to estimate the hazard of discontinuing PrEP at 7 months and through 18 months will be conducted, thus taking into account the presence of censoring due to end of study period or drop-out, including all participants who are confirmed as HIV-uninfected at enrolment and who attend at least the PrEP initiation visit (visit 1).

More specifically, PrEP persistence at 7 and 18 months will be summarized in the first instance as proportions of subjects on a given modality at those time points out of those who started on the modality and compared using a chi-square test. Additionally, Kaplan-Meier curves will illustrate the time to discontinuation by PrEP modality. Cox proportional hazards model will be used to analyse the risk of discontinuation overall, (i) regardless of modality and (ii) taking modality into account. Frailty models will account for repeated discontinuations per subject. Modality will be included as a time-varying exposure variable. Additionally, time to switching modality will be analysed using a Cox proportional hazards model, with frailty terms to account for repeated switches, if required. Models will include subject-specific characteristics that may confound the association between modality and risk of discontinuation. Different subgroups (adolescent girls and young women, intimate male partners, and gay and other men who have sex with men) can be included as a predictor in the models and additionally analysis will be repeated for sub-groups of interest. The average time to restart, the mean number of restarts for a participant and the total number of restarts across the study period will be reported and used to describe the variation in PrEP user journeys throughout the product.

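### The primary timepoint for persistence is stated two ways, and the CAB-LA hypothesis leaves both the comparator and the gap rule open

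*Protocol article*

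**What the plan says.** **Timepoint.** In the protocol article, Aims and objectives opens: "The primary clinical aim of PtC is to describe patterns of short and long-term persistence (as measured over 7 months and 18 months respectively"). The abstract's Methods paragraph is looser. It speaks of "co-primary clinical and implementation aims that include an analysis of PrEP persistence" and then gives the horizon as "over the short term (7 months) and long term (18 months), and the identification of implementation strategies".

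Table 1 separates the two. Its primary clinical aim is "1.1 To compare short term persistence (over 7 months) across PrEP modalities and PrEP overall", and among the secondary aims stands "2.1 To compare long term persistence (over 18 months) across PrEP modalities and PrEP overall". The Statistical analysis section uses the same order: "To determine the primary and secondary endpoints of short-term and durable persistence (as defined above"). The sample size paragraph powers month 7 only.

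**Hypothesis.** The comparison by product is tied to a single hypothesis, that "there will be a significantly greater persistence in the CAB LA group compared to oral PrEP and/or DapiRing". It names no timepoint. The sample size paragraph likewise joins the two comparisons with an or and powers each one singly.

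**Gap rule.** Persistence is defined under both a 7-day and a 28-day gap. Aims and objectives expects the 28-day gap to be the more realistic one locally. The Discussion says: "The PtC study as such will report on persistence using both a 7 day and 28-day visit window". Neither rule is named as the one on which the hypothesis is tested.

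**The concern.** Two current statements of the primary clinical aim disagree. An analysis plan that adopts one of them leaves the other in print, so a reader of the results could not tell from the article whether an 18-month comparison was primary or secondary.

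Separately, a claim of significantly greater persistence on CAB-LA can be reached by more than one route: over oral PrEP or over the ring, and under one gap rule or the other. If each route is tested at the usual level and any one is enough, the false-claim rate for the hypothesis exceeds that level. The groups are self-selected and comparator numbers are not fixed, so it matters that the test carrying the claim is identified beforehand.

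**Working it through.** **1. Timepoint, side by side**

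| Place in the protocol article | Month 7 | Month 18 |
|---|---|---|
| Aims and objectives, opening sentence | primary | primary |
| Abstract, Methods | within co-primary aims | within co-primary aims (loosely) |
| Table 1, aims 1.1 and 2.1 | primary | secondary |
| Sample size calculation | powered | not mentioned |
| Statistical analysis | primary (by word order) | secondary (by word order) |

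Three places agree on month 7 alone. One clearly says otherwise, and one does so loosely.

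**2. The plan's own power figures**

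Stated: more than 85% power for an 8-point difference with 900 on CAB-LA, and more than 80% for 11 points with 700 vs 200. For 85%, neither the comparator size nor the base rate is given, so the figure can only be bracketed. The test is the pooled two-proportion (chi-square) test, two-sided 5%. The level is read from the stated 95%; sidedness is an assumption.

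Power = Φ[(Δ − z·SE₀)/SE₁], with SE₀ = √[p̄(1−p̄)(1/n₁+1/n₂)] and SE₁ = √[p₁(1−p₁)/n₁ + p₂(1−p₂)/n₂].

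At the least favourable base rate (54% vs 46%):
- 900 vs 900: 92.5%
- 900 vs 600: 86.0%
- 900 vs 450: SE₀ = 0.02886, SE₁ = 0.02877, (0.08 − 1.960 × 0.02886)/0.02877 = 0.815, power 79.2%
- 900 vs 200: 53.6%

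About 573 per comparator give 85% at that base rate. The 700 vs 200 case gives 78.6% at worst (55.5% vs 44.5%) and passes 80% at several other base rates. The stated figures are therefore attainable for a single comparison. They make no allowance for a second one.

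**3. Number of routes**

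2 comparators × 1 gap rule = 2. With 2 gap rules at month 7, 4. With month 18 also primary, 8.

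**4. False claims in favour of CAB-LA when there is no difference**

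The hypothesis is directional, so only z > 1.96 counts; the nominal level is 2.5% per test.

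Assumptions: 900 on CAB-LA; comparators from 450/450 to 700/200; 28-day persistence 50%; 50% to 85% of those also persistent under the 7-day rule.

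- *Two comparators, one gap rule.* The shared CAB-LA group correlates the tests: ρ = √[n₁/(900+n₁) × n₂/(900+n₂)], which is 0.33 for 450/450 and 0.28 for 700/200. The chance of at least one false claim is 4.7–4.8%. If the tests were independent it would be 1 − 0.975² = 4.9%.
- *Either gap rule at month 7.* The 7-day status is nested in the 28-day status, with correlation √[p₇(1−p₂₈)/(p₂₈(1−p₇))]. That is 0.58 for p₇ = 0.25 and 0.86 for p₇ = 0.425. The chance over four tests is 6.9–8.3%.
- *Month 18 also primary.* Simulation with correlated month-7 and month-18 status gives about 12–14% over eight tests. This needs further assumed 18-month rates.

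A wider set of assumed rates (28-day persistence 55–60%, 7-day 30–50%) gives about 5%, 6.6–8.5% and 11–14%.

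**The case against.** The strongest reply is that the article states no rule for declaring success. It says only that the comparison will be related to a hypothesis. The and/or covers comparators, not gap rules, and the Discussion presents the two windows as parallel reporting, to show how the window affects the result. The opening sentence of the aims says describe, not compare. Multiplicity procedures are commonly left to the analysis plan, which is not shown.

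Much of this stands. A reader might infer that any one of four to eight tests counts as success, with a false-positive rate of about 14–17% or 25–28%. The documents do not support that:
- Those rates count any two-sided p < 0.05, including results showing CAB-LA worse, which cannot support a hypothesis of greater persistence. Counting only favourable results roughly halves them.
- That either gap rule suffices follows only from neither being ranked; no sentence says so.
- Eight tests requires month 18 to be primary, against Table 1, the sample size paragraph and the Statistical analysis section.

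The absence of a multiplicity procedure from the article is likewise no fault in itself.

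What the reply does not remove is the text that is there. The primary aim is stated two ways. The hypothesis claims a significant difference, is backed by a power statement and a named test, and by its own wording is met through either comparator.

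**Conclusion.** The point holds as an inconsistency in the primary timepoint and an open hypothesis, with moderate inflation of error. The and/or alone roughly doubles the directional error, from 2.5% to about 5%. Leaving the gap rule open as well takes it to about 7–8% at month 7. The 12–14% figure applies only if the opening sentence of the aims is preferred to Table 1, which is the weaker reading.

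The sizes rest on an assumed two-sided 5% level per test and on assumed persistence rates and group sizes. They changed little over the ranges tried. The timepoint conflict needs no assumption. The matter should be corrected before the comparative analysis, and nothing about the conduct of the trial has to change.

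**What to change.** 1. Reword the opening of Aims and objectives, and the abstract, to match Table 1: month 7 primary, month 18 secondary.
2. Name one gap rule for the hypothesis test, and report persistence under the other as a supportive estimate with a confidence interval. Both windows still appear, as the Discussion intends.
3. Replace the and/or with two named comparisons, CAB-LA vs oral PrEP and CAB-LA vs ring, tested with Holm or in a prespecified order. The order is the sponsor's to choose, since nothing in the article ranks oral PrEP above the ring.

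**Cost.** Under Holm the smaller p-value must meet 2.5%, and the other may then be tested at 5%. The loss for a single comparison is therefore at most that of a flat 2.5% level. For an 8-point difference at the least favourable base rate:
- 900 vs 450: (0.08 − 2.241 × 0.02886)/0.02877 = 0.53, so 79.2% falls to 70.3%, about 9 points
- 900 vs 900: 92.5% falls to 87.6%, about 5 points
- 900 vs 200: 53.6% falls to 42.4%, about 11 points, from a level already low

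A fixed order costs the first comparison nothing, but the second cannot be claimed if the first fails. The rest is wording.
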